#### Statistical analysis

This study will require several statistical analyzes. The main analysis will focus on the randomized phase of the study (from M6 to M18).

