### Procedures

In practice, each center uses two investigators in addition to the physical therapist for the GSC group. One is a clinical assessor (physician or physiotherapist) who remains blinded to the participant group; the other is the coordinator whose role is to organize the five semi-annual evaluations at D1, M6, M12, M18, M24. The coordinator will be unblinded and will be in contact with the participant’s physicians and with the physiotherapist involved in the GSC for the study center (for those participants in the GSC group). The coordinating investigator, after receiving the result of the randomization at the M6 visit, will:inform the participant and the physiotherapist who will apply the GSC method, for those participants randomized in the GSC group,notify the participant to continue with the usual therapy without further details, for those participants randomized in the CONV group.

Pre-inclusions will take place during a regular clinic visit. Participants meeting the selection criteria will be invited to participate in the protocol. A written descriptive documentation will be provided to them and potential study subjects will have at least 2 weeks to decide about participation. The informed consent will be signed and collected on the Day 1 visit of the study.

Phase 1 will then be a 6-month prospective follow-up period - with visits at D1 and M6 (Month 6) - to evaluate any changes under conventional community-based therapy. The same blinded investigator will evaluate participants at all follow-up visits, D1, M6, M12, M18, M24 (Table 1). At each visit, specific attention will be paid to any signs suggesting recurrent strokes with, if necessary, additional prescription of brain imaging. Should there be a diagnosis of recurrent stroke since study enrolment (calling for neuroradiologist opinion if needed), study participation will be discontinued and an Adverse Events form and Study Termination form will be filled out.

**Table 1 Tab1:** Template of recommended content for the schedule of enrolment, interventions, and assessments

	D1	M6	M12	M18	M24
Verification of inclusion and non-inclusion criteria	x				
Signature of written consent	x				
Full neurologic assessment	x				
Randomization		x			
Inventory of concomitant, local and systemic medical treatment s	x	x	x	x	x
Inventory of technical aids	x	x	x	x	x
Inventory of patient suppor t (caregivers, equipment)	x	x	x	x	x
Comfortable and maximal ambulation speed over 10 m s	x	x	x	x	x

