### Randomization procedure

The randomization list will be computer-generated by a statistician from the Clinical Research Unit of Paris-Est Créteil University, independent from the study. The randomization number for each participant will be requested by the evaluating investigator (blinded) at the end of Visit 2 (M6) and then transmitted electronically to the referring coordinator (unblinded) of the center. Each participant will be randomized into one of the two treatment groups: the CONV group (Conventional Therapy) and the GSC group (Guided Self-rehabilitation Contract). Randomization will be stratified by center.

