#### Descriptive analysis of the first phase

For Phase 1 (Day 1 to M6), descriptive analysis will explore:participant characteristics: age, sex, etiology of stroke, presence of significant sensory deficit, apraxia, neglect at Day 1 and M6.changes in function over the first 6 months of follow-up: ambulation speed, upper limb function (MFS) and secondary criteria.the current conventional therapy treatment: frequency of sessions with the community-based physiotherapist, number of visits and costs. The sum of the monthly frequency during the first 6 months of rehabilitation and the monthly cost of these sessions will be estimated for all 124 participants together. Comparisons will then be made between different levels of severity at onset and different age groups.

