#### Analysis of the randomized study

The analysis of the randomized study will be carried out based on intent to treat and per protocol.

The primary and secondary criteria and their changes from M6 to M18 will be compared between the two groups using mixed models. The changes will also be compared at M24, i.e. 6 months following the end of the study treatment. These same analyzes will be carried out by subgroups, comparing the availability of a psychological follow-up or not, ie in the participants recruited by the Mondor-Lariboisière centers versus those of the other centers.

A multivariable analysis will be carried out by considering the characteristics of the patients (age, sex), the center, the initial severity parameters of the disease (sensory disturbances) or time since stroke, as well as the availability or not of a psychologist.

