#### Pre−/post-analysis

With patients being their own control, the changes in various functional parameters during the first 6 months of follow-up with conventional therapy (from Day 1 to M6) will be compared with the changes in these same parameters:during the randomized study between M6 and M12during the randomized study between M12 and M18and during follow-up between M18 and M24.

The mean changes and the rate of progression over periods of 6 months will be compared. These same comparisons will be realized in subgroups according to the randomization group, but also depending on any specific psychotherapeutic management (for 44 participants, in the two centers involved).

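### The main randomised comparison does not name the D1 value of either co-primary outcome; adding it as a second pre-randomisation covariate is a cheap, optional gain in precision

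*Protocol article*

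**What the plan says.** Under Statistical analysis, the protocol article states: "The main analysis will focus on the randomized phase of the study (from M6 to M18". Analysis of the randomized study adds: "The primary and secondary criteria and their changes from M6 to M18 will be compared between the two groups using mixed models". It does not list the covariates of those mixed models.

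A further multivariable analysis is described there: "A multivariable analysis will be carried out by considering the characteristics of the patients (age, sex), the center, the initial severity parameters of the disease". The example of severity given is sensory disturbance, with time since stroke and access to a psychologist also named. No outcome value from D1 appears in the list.

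On timing, Randomization procedure says: "The randomization number for each participant will be requested by the evaluating investigator (blinded) at the end of Visit 2 (M6". Procedures says: "The same blinded investigator will evaluate participants at all follow-up visits, D1, M6, M12, M18, M24 (Table 1". Table 1 marks 10 m ambulation speed and the MFS at all five visits.

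The D1 values have two stated uses. Descriptive analysis of the first phase covers "changes in function over the first 6 months of follow-up: ambulation speed, upper limb function (MFS) and secondary criteria". Under Pre−/post-analysis, "the changes in various functional parameters during the first 6 months of follow-up with conventional therapy (from Day 1 to M6) will be compared"; the comparators are the later six-month periods, and this is also done by randomised group.

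**The concern.** D1 and M6 both precede randomisation, and both co-primary outcomes are scheduled at both visits. A comparison that starts at M6 relies on one visit to represent the patient's starting level, so the visit-to-visit error of that one visit stays in the residual. A second pre-randomisation value can remove part of it. Because D1 is measured before allocation, using it cannot bias the comparison of Guided Self-rehabilitation Contract (GSC) with conventional therapy (CONV).

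Neither stated use of D1 helps that comparison. One is descriptive. The other compares periods within patients. What is at stake is the width of the confidence interval for the GSC-CONV difference at M18, using data the trial already plans to collect.

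**Working it through.** **Inputs from the documents.** Visits at 0, 6 and 18 months; randomisation at M6; 62 per group. For the MFS: mean 4.4, SD 1.9, improvement of 30% against 10%, so a difference of 4.4 × 0.20 = 0.88. For walking speed: mean 0.63 m/sec, SD 0.43, improvement of 50% against 10%, so a difference of 0.63 × 0.40 = 0.252 m/sec.

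**Inputs assumed.** All between-visit correlations. The documents give none, so a range is shown.

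**The plan's own figures.** The plan gives no precision figure for this comparison. Its sample sizes serve only as the starting point for power. With an unadjusted two-sided 5% test at 80% power, the walking-speed inputs give 46.7 per group (t-based), which matches the stated 47. The MFS inputs give 74 per group rather than 62, and 62 per group gives 73.2% power. That mismatch is a separate matter.

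**Formulas.** Write c for the D1-M6 correlation, b for M6-M18 and a for D1-M18. In units of SD²:
- residual variance adjusting for M6 only: V1 = 1 − b²
- residual variance adjusting for M6 and D1: V2 = 1 − (a² + b² − 2abc)/(1 − c²)

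**Case 1: all visits correlate equally at r.** V1 = 1 − r², V2 = 1 − 2r²/(1 + r), and the ratio is V2/V1 = (1 + 2r)/(1 + r)².

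| r | Ratio | Variance reduction |
|---|---|---|
| 0.7 | 2.4/2.89 = 0.830 | 17.0% |
| 0.8 | 2.6/3.24 = 0.802 | 19.8% |
| 0.9 | 2.8/3.61 = 0.776 | 22.4% |

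**Case 2: the latent state drifts and each visit adds noise.** With latent correlation φ per 6 months and reliability k: c = kφ, b = kφ², a = kφ³. For φ = 0.95 and k = 0.85, c = 0.8075, b = 0.7671 and a = 0.7288, so V1 = 0.4115, V2 = 0.3772 and the ratio is 0.917.

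| φ | k = 0.85 | k = 0.90 | k = 0.95 |
|---|---|---|---|
| 0.95 | 0.917 | 0.935 | 0.966 |
| 0.90 | 0.960 | 0.973 | 0.989 |

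The variance reduction is therefore about 1% to 8%.

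**Case 3: pure first-order autoregressive decay (k = 1).** Here a = bc, so D1 adds nothing once M6 is in the model: ratio 1.000, reduction 0%.

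**Averaging is a different proposal.** Under pure decay with φ = 0.95, the variance of a change from M6 is 0.195. From the mean of D1 and M6 it is 0.2151, which is 10.3% larger. Separate coefficients avoid this risk.

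**Effect on power at 62 per group** (normal approximation, stated effects; M6-adjusted, then M6 plus D1):
- MFS, equal correlation 0.5: 84.6% to 88.5%
- MFS, equal correlation 0.7: 95.1% to 97.7%
- MFS, equal correlation 0.8: 99.0% to 99.8%
- MFS, the six drift scenarios: a gain of less than 1 percentage point in each
- Walking speed: at least 99.4% without D1 in the equal-correlation cases from 0.7 to 0.9 and in all six drift scenarios

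**The case against.** The strongest reply is that nothing here is wrong. M6 is the value at randomisation and a proper baseline. The article says the main analysis will focus on M6 to M18, which names the comparative phase, and it leaves the covariates of the mixed models open. A model that includes D1 would fit that wording, and such detail is commonly left to an analysis plan that is not shown. The multivariable list omits the D1 outcome, but it omits the M6 outcome too, so it does not show that D1 was singled out.

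All of this stands. A reader might infer that the trial discards D1 or that the plan rules it out of the main model. The documents do not support either: D1 has two planned uses, and the model is unspecified.

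The size of the gain can also be challenged. Equal correlation requires D1 to predict M18 over 18 months as well as M6 does over 12. Two features of the protocol could shrink the gain further. Eligibility limits both co-primaries and is verified at D1, which narrows the spread of the D1 values. Tapering of systemic antispastic agents is recommended between D1 and M6; a fitted coefficient can absorb a common shift, but shifts that differ between patients would weaken what D1 adds. In the other direction, patients are more than a year post stroke and Phase 1 is meant to assess clinical stabilisation. If they are stable, the larger gains become more plausible.

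The objection does not remove the basic point: the second value is already scheduled, is safe to use, and is not named for the comparison it could sharpen.

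**Conclusion.** The point holds as an optional efficiency gain. As written, the main comparison runs from M6 to M18 without naming the D1 value of either co-primary outcome. Adding D1 to an M6-adjusted model would lower residual variance by about 17% to 22% under equal correlations of 0.7 to 0.9, by about 1% to 8% under the drift-plus-noise settings tried, and by 0% under pure autoregressive decay. These figures rest wholly on assumed correlations.

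A reader might take the upper end as a saving of 20% to 29% more patients (1/0.830 = 1.20; 1/0.776 = 1.29). That is the best case among those tried and should not be presented as the expected loss. The relative saving is also greatest where M6 adjustment already brings power for the assumed effects close to its ceiling. The practical benefit there is narrower intervals and some protection if the true effect is smaller than planned.

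**What to change.** State before analysis that the primary mixed model for each co-primary outcome includes the D1 and M6 values as two separate covariates with freely estimated coefficients, not their average, and that the GSC-CONV difference at M18 is the primary contrast. Apply the same rule to each secondary criterion measured at both visits.

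An alternative is a longitudinal model in which the D1 and M6 means are constrained equal between arms and the covariance is unstructured. The two are essentially equivalent only with complete data. Over two years, with participation ending on recurrent stroke, complete data should not be assumed, so one of them should be named in advance.

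The cost is one sentence of wording and about one degree of freedom. No new visit or measurement is needed.

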#### Descriptive analysis of the first phase

For Phase 1 (Day 1 to M6), descriptive analysis will explore:participant characteristics: age, sex, etiology of stroke, presence of significant sensory deficit, apraxia, neglect at Day 1 and M6.changes in function over the first 6 months of follow-up: ambulation speed, upper limb function (MFS) and secondary criteria.the current conventional therapy treatment: frequency of sessions with the community-based physiotherapist, number of visits and costs. The sum of the monthly frequency during the first 6 months of rehabilitation and the monthly cost of these sessions will be estimated for all 124 participants together. Comparisons will then be made between different levels of severity at onset and different age groups.

#### Analysis of the randomized study

The analysis of the randomized study will be carried out based on intent to treat and per protocol.

The primary and secondary criteria and their changes from M6 to M18 will be compared between the two groups using mixed models. The changes will also be compared at M24, i.e. 6 months following the end of the study treatment. These same analyzes will be carried out by subgroups, comparing the availability of a psychological follow-up or not, ie in the participants recruited by the Mondor-Lariboisière centers versus those of the other centers.

A multivariable analysis will be carried out by considering the characteristics of the patients (age, sex), the center, the initial severity parameters of the disease (sensory disturbances) or time since stroke, as well as the availability or not of a psychologist.

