### Statistical methods

#### Sample size

With respect to the Modified Frenchay Scale, based on an average score of 4.4 ± 1.9 in a similar population, [82] the alternative hypothesis (H1) is an improvement of 30% in the GSC group versus a 10% improvement in the CONV group. To demonstrate this hypothesis with a bilateral 80% power and an alpha score of 5%, *n* = 62 subjects per group are required for a total of 124 participants.

With respect to the maximal ambulation speed over 10 m, with an assumed baseline ambulation speed of 0.63 ± 0.43 m/sec and with the hypothesis of a 50% improvement in the GSC group versus a 10% improvement in the CONV group, at least *n* = 47 participants per group are required using a bilateral power of 80% with an alpha of 5% [47]. A total of 124 patients will thus be included in the protocol. This number should also allow sufficient power to evaluate secondary criteria, including a description of the monthly frequencies of the rehabilitation sessions, of the required aids and allowances and therefore an estimation of the cost from the point of view of the health insurance and the State.

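### The randomised-phase analysis names two comparisons per co-primary endpoint without saying which decides, and does not name the M6 value or centre in the primary model

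*Protocol article*

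**What the plan says.** All references are to the protocol article.

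- **Main comparison** (Analysis of the randomized study): "The primary and secondary criteria and their changes from M6 to M18 will be compared between the two groups using mixed models". No fixed effects, random effects or handling of M6 are listed. Both intention-to-treat and per-protocol analyses are planned.
- **Covariates** (next paragraph but one, same section): "A multivariable analysis will be carried out by considering the characteristics of the patients (age, sex), the center", followed by initial severity, with sensory disturbances as the example, or time since stroke, and psychologist availability. The M6 value of the outcome is not in the list.
- **Stratification** (Randomization procedure): "Randomization will be stratified by center". The randomisation number is requested at the end of the M6 visit, so the M6 assessment precedes allocation.
- **Sample size**, Modified Frenchay Scale (MFS): "based on an average score of 4.4 ± 1.9 in a similar population"; the alternative hypothesis "is an improvement of 30% in the GSC group versus a 10% improvement in the CONV group"; "with a bilateral 80% power and an alpha score of 5"%; 62 "subjects per group are required for a total of 124 participants". Walking speed is planned "with an assumed baseline ambulation speed of 0.63 ± 0.43 m/sec", with 50% against 10% improvement and at least 47 per group. No M6–M18 correlation is given.

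**The concern.** A test of M18 values and a test of M6–M18 changes answer the same treatment question with different precision. Which is stronger depends on r: below 0.5 the raw value has the smaller variance, above 0.5 the change does. With both announced and neither ranked, the deciding result could be chosen after the data are seen, for each of two co-primary endpoints.

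The M6 value of the outcome is likely to be the best available predictor of M18. It is measured before randomisation and already collected. A raw-value comparison carries any chance M6 imbalance into the estimate. A change score subtracts the whole M6 value, which over-corrects when r is below 1. Adjustment uses the M6 value with the weight the data support.

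Centre was used to constrain the allocation, so it would normally be in the primary model as well, and the article places it only in a secondary one. Precision matters most for the MFS, where the stated sample size falls short of its own power target.

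**Working it through.** **Inputs.** From the Sample size section: MFS mean 4.4, SD 1.9, two-sided 5% level, 80% power, 62 per group. The difference is (30% − 10%) × 4.4 = 0.88, so d = 0.88/1.9 = 0.463. The correlation r is an assumption, so a range is shown. Powers are from the two-sample t-test.

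**Step 1: the plan's own figure.** Solving for n at d = 0.463 and 80% power gives 74.2, so 75 per group (74 by the normal approximation), not 62. At 62 per group the power is 72.5% (73.2% by the normal approximation). For walking speed the difference is (50% − 10%) × 0.63 = 0.252 with SD 0.43; the solution is 46.7, so the stated 47 reproduces, and power at 62 per group is about 90%.

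**Step 2: effective SDs, reading 1.9 as the SD of values at M6 and at M18.**

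- Raw M18 value: 1.9
- Change M6–M18: 1.9 × √(2(1 − r))
- M18 adjusted for M6: 1.9 × √(1 − r²)

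The adjusted variance is therefore 1 − r² of the raw variance and (1 − r²)/(2(1 − r)) = (1 + r)/2 of the change variance. Neither ratio exceeds 1.

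**Step 3: MFS power at 62 per group, difference 0.88.**

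| r (assumed) | SD of change | SD adjusted | Raw | Change | Adjusted |
|---|---|---|---|---|---|
| 0.3 | 2.25 | 1.81 | 73% | 58% | 76% |
| 0.41 | 2.06 | 1.73 | 73% | 65% | 80% |
| 0.5 | 1.90 | 1.65 | 73% | 73% | 84% |
| 0.6 | 1.70 | 1.52 | 73% | 82% | 89% |
| 0.7 | 1.47 | 1.36 | 73% | 91% | 95% |

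The adjusted analysis reaches 80% from r of about 0.41. The unadjusted change score reaches it from about 0.58.

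**Step 4: the other reading of 1.9.** The article does not say which SD 1.9 is. If it is the SD of change, the change comparison has 73% power whatever r is, and the adjusted SD is 1.9 × √((1 + r)/2). At r = 0.5 that is 1.65 (84% power); at r = 0.7 it is 1.75 (79%). Adjustment still helps but does not always reach 80%.

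**Centre.** No between-centre variance is given, so no figure can be attached to including it.

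**The case against.** The strongest reply is that the article gives only the model class. A reader might infer that the primary analysis is unadjusted for M6 and for centre; the text does not say so. It neither includes nor excludes them. A mixed model that takes M6 as a repeated response with a common mean across groups can be about as efficient as adjustment for M6, and a random centre effect is ordinary in such models. Covariate lists are commonly left to a fuller document that is not shown. The raw and change columns above are two-sample tests, not the planned model. This stands: the table shows what is at stake between specifications, not a loss the trial is known to incur.

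A reader might also infer that adjustment would restore the missing MFS power. That is not supported as a general statement. On the cross-sectional reading, adjustment makes the difference between missing and reaching 80% by comparison with the change score only for r between about 0.41 and 0.58. Below that range it falls short; above it the change score gets there alone. If 1.9 is the SD of change, it falls short at r = 0.7. Walking speed already has about 90% power, so little hangs on it there.

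Nor is M6 or centre ignored altogether: the change score uses M6, and centre is in the multivariable analysis.

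What the reply does not remove is in the text itself. Two comparisons are stated without a ranking, and where covariates are listed, centre is placed in a separate analysis and the M6 outcome value is absent.

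**Conclusion.** The point holds as an improvement that should be made, not as proof of an unadjusted analysis. The article leaves the deciding comparison open between values and changes, names the stratification factor only outside the main comparison, and names the M6 outcome value as a covariate nowhere. A single adjusted M18 contrast is, asymptotically, at least as precise as either stated comparison.

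For the MFS, on the cross-sectional reading of 1.9, the gain over raw values runs from about 4 percentage points of power at r = 0.3 to about 22 at r = 0.7, and over change scores from about 18 down to about 4. These figures rest on an assumed r, equal SDs at M6 and M18, the stated effect, and 62 analysed patients per group. The sample-size discrepancy is a separate error that the choice of model does not correct.

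**What to change.** Prespecify one primary model for each co-primary endpoint:

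- response: the M12 and M18 values;
- fixed effects: treatment by visit, M6 value by visit, and centre;
- patient as the repeated unit;
- the treatment contrast at M18 as the single primary estimate.

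Label the remaining value and change comparisons, and the multivariable analysis, as supportive.

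The cost is wording in the protocol or analysis plan, fixed before unblinded data are seen. Both outcomes are already scheduled at M6, M12 and M18, and centre is known from randomisation, so no extra patients or visits are needed. Separately, restate or justify the 62 per group for the MFS, say which SD 1.9 is, and give the assumed M6–M18 correlation if the restated power is to rely on adjustment.

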## Objectives

The primary objective of this study is to evaluate changes in lower limb and upper limb motor function after 1 year of Guided Self-rehabilitation Contract compared to conventional therapy alone, at a chronic stage following stroke.

The secondary objectives include the evaluation of: i) quality of life at the end of 1 year with each of the two treatment modalities; ii) direct socioeconomic costs of the two physical treatments from the point of view of the health coverage system; iii) persistence of lower limb and upper limb motor function changes 6 months after the end of the one-year experimental study period; iv) amount of self-rehabilitation in the experimental group over 12 months; v) current, real-life amounts of conventional rehabilitation provided for chronic hemiparesis in the French health system. vi) psychological and occupational therapy endpoints with the two treatments, for a sub-group of 44 patients.

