The secondary outcome measures are:Ambulation speed, step length and cadence during the ambulation test over 10 m (AT10) barefoot at comfortable speed without technical aid, and step length and cadence during AT10 at maximal speed [61];Ambulation speed, step length, cadence and physiological cost index over a 2-min ambulation test at maximal speed without technical aid [72];Subjective self-assessment of perceived function (DAS) indicating the degree of functional incapacity evaluated by the patient for hygiene and dressing activities, pain and cosmesis [70, 73];Global test of functional dependency (Barthel Index) [74];Quality of life (SF 36) [75, 76];Anxiety and depression test (Geriatric Depression Scale, GDS) [77];Evaluation by questionnaires, completed by the patient (and/or a third person), on the weekly frequency and duration of the conventional rehabilitation sessions and the amount of professional help received at home during the study period, to estimate the direct costs from the point of view of the health coverage system;Estimation of the total cost of healthcare, including medical, socio-medical, allowance cost, combining the points of view of the medical insurance and of the State, to encompass all paying institutions;Evaluation of the amount of self-rehabilitation in the GSC group, through the filling ratio of diaries over 12 months [28], (www.i-gsc.com);Evaluation of functioning and home adaptation by an occupational therapist and by questionnaires, in a sub-group of 44 participants in two of the six study centers;Evaluation of the psychological adjustment of the patient, by a study psychologist in the same sub-group of 44 participants in two of the six study centers, to assess the required psychological resources and the need for psychological support. Each of these participants will be contacted for a first visit and offered to consult with the psychologist for the two-year study period. The frequency of encounters will be adjusted to the need of each patient.

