### Setting and recruitment

This multicenter trial involves six French centers (the medical centers in Saint-Etienne, Reims, Bordeaux, Toulouse, and Henri Mondor and Lariboisière university hospitals in Paris). Each of these centers admits > 100 cases/year of patients with moderate to severe stroke-induced hemiparesis for specialized rehabilitation and will recruit 20 to 24 patients. A 3-year time-frame is planned for the study, each center starting the study once the total expected number of participants to be enrolled are lined up. The objective is thus to run the protocol simultaneously for all participants of each center, to make optimal use of the study therapist’s time (GSC group).

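### Repeating the GSC-versus-CONV comparisons inside the psychologist centres and inside the other centres does not test whether the GSC effect depends on psychological follow-up; a treatment-by-subgroup interaction term would

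*Protocol article*

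**What the plan says.** The Protocol article, under Analysis of the randomized study, first sets the between-arm analysis: "The primary and secondary criteria and their changes from M6 to M18 will be compared between the two groups using mixed models". It adds a comparison at M24 and then continues: "These same analyzes will be carried out by subgroups, comparing the availability of a psychological follow-up or not". The subgroups are defined by centre: "in the participants recruited by the Mondor-Lariboisière centers versus those of the other centers".

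Outcome measures gives the size of the psychologist subgroup: "in the same sub-group of 44 participants in two of the six study centers". With 124 patients in total, about 80 remain in the other four centres.

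The Pre−/post-analysis section uses the same split: "These same comparisons will be realized in subgroups according to the randomization group, but also depending on any specific psychotherapeutic management".

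Elsewhere, psychologist availability appears in the multivariable analysis, as one of the characteristics to be considered beside age, sex, centre and severity. No interaction with treatment is named. The tests under Statistical tests and software used are for subgroups formed on starting clinical variables or demographic data; they do not supply a test of whether the GSC effect differs between the two sets of centres.

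**The concern.** The stated purpose is to compare patients with and without access to psychological follow-up. For a treatment trial the useful question is whether the GSC-minus-CONV difference is larger in one set of centres than in the other. That is an interaction: a difference between two differences, with its own standard error.

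Running the GSC-versus-CONV comparison once in about 22 patients per arm and once in about 40 per arm produces two answers to another question, namely whether GSC differs from CONV in each set. The larger set has more power whatever the truth. If one result is significant and the other is not, the natural but mistaken conclusion is that GSC works only with, or only without, psychological follow-up. This is a pre-planned analysis, so such a result could carry weight in the report.

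**Working it through.** **Inputs from the Protocol article**
- Total 124; psychologist subgroup 44; remainder 124 − 44 = 80.
- Randomisation is stratified by centre and the planned arms are equal, so I assume 1:1 allocation within subgroups: 22 + 22 and 40 + 40.
- Modified Frenchay Scale (MFS), Sample size section: mean 4.4, SD 1.9, improvement 30% versus 10%. Difference = 0.20 × 4.4 = 0.88; d = 0.88/1.9 = 0.463.
- Maximal walking speed, same section: mean 0.63, SD 0.43 m/s, improvement 50% versus 10%. Difference = 0.40 × 0.63 = 0.252; d = 0.252/0.43 = 0.586.
- Two-sided 5% is stated for the sample size only. Its use in the subgroup comparisons is my assumption.

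**The plan's own figures.** From n = 2(1.960 + 0.842)² SD²/difference², walking speed gives 46 per group (47 with the t distribution), which matches the stated 47. MFS gives 74 (75 with t), not the stated 62. That mismatch is a separate matter. An SD of 1.75 would give 62; using it below moves the MFS result only from 51% to 53%.

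**Step 1: identical true effect, separate two-sample t-tests.** With power p₁ in the smaller and p₂ in the larger subgroup, the chance that exactly one is significant is p₁(1 − p₂) + p₂(1 − p₁).

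| Outcome and SD | p₁ (22 per arm) | p₂ (40 per arm) | Exactly one significant |
|---|---|---|---|
| MFS, stated SD 1.9 | 0.323 | 0.534 | 0.323 × 0.466 + 0.534 × 0.677 = 0.512 |
| Walking speed, stated SD 0.43 | 0.476 | 0.735 | 0.476 × 0.265 + 0.735 × 0.524 = 0.511 |

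A simulation of 40,000 trials agrees: 51.4% and 51.2%. For MFS, 36.3% of trials are significant only in the larger subgroup and 15.1% only in the smaller.

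**Step 2: sensitivity.**
- Subgroup size. The Setting and recruitment section says each centre "will recruit 20 to 24 patients", so two centres give 40 to 48 patients. Splits of 40/84 and 48/76 give 50% to 52% for MFS and 49.5% to 53% for walking speed.
- SD of change. The analysis is of change from M6 to M18, whose SD is SD × √(2(1 − r)) for an M6–M18 correlation r. The documents give no r. At r = 0.5 the SD of change equals the stated SD, so Step 1 holds. Assumed higher values give:

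| Assumed r | MFS: SD, p₁, p₂, exactly one | Walking speed: SD, p₁, p₂, exactly one |
|---|---|---|
| 0.7 | 1.472, 0.491, 0.752, 50% | 0.333, 0.689, 0.916, 34% |
| 0.8 | 1.202, 0.660, 0.899, 37% | 0.272, 0.851, 0.984, 16% |

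- No true effect: 2 × 0.05 × 0.95 = 9.5%.

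**Step 3: interaction test instead.** By construction it signals a difference in 5% of trials when the effects are equal (simulated 5.2% for MFS, 5.0% for walking speed). Its standard error is SD × √(2/22 + 2/40): 0.713 for MFS and 0.161 m/s for walking speed. If the two subgroup effects differed by the whole design effect, its power at the stated SDs would be Φ(0.88/0.713 − 1.96) = 23% for MFS and Φ(0.252/0.161 − 1.96) = 35% for walking speed.

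**The case against.** The strongest reply is that this is a condensed article and the analysis plan is not shown. The model, the significance level and the exploratory status of a subgroup analysis are often settled in that plan. The wording also speaks of comparing one set of centres with the other, after naming mixed models, so a formal comparison between subgroups is a possible reading. Nowhere does the protocol say that a significant result in one subgroup and not in the other will be taken as a difference.

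Part of this stands. The 51% depends on that reading and on an assumed 5% level, and it falls when the SD of change is smaller than the stated SD. But the article is not merely silent. It names the procedure, which is to repeat the same between-arm analyses by subgroup, and it gives no other means of comparing the subgroups. That procedure does not answer the question it is meant to serve.

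Three stronger readings are tempting and are not supported:
- That every subgroup comparison is planned at 5%, so the chance of a false efficacy claim is inflated. The 5% appears only for the sample size, and no text lets a subgroup result support efficacy; the primary objective is the overall comparison.
- That the protocol claims adequate power in the 44 patients. The sentence "This number should also allow sufficient power to evaluate secondary criteria" goes on to session frequencies, aids and costs. It makes no claim about a subgroup efficacy test.
- That the objective on "psychological and occupational therapy endpoints with the two treatments, for a sub-group of 44 patients" is such a test. It concerns outcomes measured in those patients, not a difference in the GSC effect.

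It is also fair to object that the interaction test has low power and cannot isolate psychological follow-up, since the subgroups are sets of centres. That is a reason for modest claims. Separate tests share the same confounding with centre and add a misleading contrast in power.

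**Conclusion.** The point holds in a limited form. The described subgroup analysis does not test whether the GSC effect differs with psychological follow-up. If the separate results are set side by side, an identical effect would look different in about 51% of trials for each co-primary at the design effects and stated SDs, against about 5% for an interaction test. The 51% is conditional, not a general rate. It assumes 22 and 40 patients per arm, two-sided 5% tests, and that significance in only one subgroup is read as dependence. With an assumed M6–M18 correlation of 0.8 it is about 37% (MFS) and 16% (walking speed), and with no effect 9.5%; all of these remain above 5%. The figures apply to the between-arm analysis and not to the within-patient pre/post comparisons, where only the labelling matters.

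**What to change.** In Analysis of the randomized study, replace the repeated subgroup comparisons with one treatment-by-subgroup term (two psychologist centres versus the other four) in the full-sample mixed model for each co-primary at M18. Report its estimate with a 95% confidence interval. Give the GSC-minus-CONV difference within each subgroup as an estimate with its interval. Label these results, and the matching split in Pre−/post-analysis, exploratory. State that the test has low power (about 23% for MFS and 35% for walking speed at the stated SDs, even for a difference as large as the whole design effect) and that it cannot separate psychological follow-up from other differences between centres.

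The cost is one model term and a few sentences; no extra patients or data are needed. The downside is that most real differences of plausible size will go undetected, so the subgroup results can only be presented as descriptive.
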